## 2. Subsequent Visits

Follow-ups will be online only. Participants in both groups will be asked to complete questionnaires and tasks regarding mental health and quality of life and work (**Table 3**). Participants will be asked to weigh themselves, provide saliva (in the morning) and stool samples as outlined above. Two-week and 4-week assessments should take about 5 minutes to complete and the 6-week and 12-week assessment about 30 minutes. In the unlikely event that there are participants that default from completing the online questionnaires and have not contacted us, a researcher will make two attempts within 3-days to phone the participant directly to administer the PHQ-9 (primary outcome) over the phone.

We will invite about 20 participants to a Teams call one-to-one interview to discuss their experiences of trying to follow the diet assigned to them, the support on offer, and the perceived effects of it on their wellbeing. We will select participants to achieve a range based on their adherence to the diet and their response as measured by change in PHQ-9. We will analyse these interviews using simple content analysis. We anticipate interviews lasting up to 30 minutes. We will audio record them prior to analysis then destroy the recordings once the analysis is complete and we are confident of the meaning. The interviews will be audio only because both participants will turn off their video function. This will allow us to use the automatic transcription in Teams to enable us to use anonymised quotes in the write-up.

**Table 3: Study schedule and follow-up assessments**

| Outcome measures | Baseline assessment (consent to the study) | 2 weeks follow-up assessment | 4 weeks follow-up assessment | 6 weeks follow-up assessment | 12 weeks follow-up assessment |
|------------------|--------------------------------------------|------------------------------|------------------------------|------------------------------|-------------------------------|
| PHQ-9            | ✓                                          | ✓                            | ✓                            | ✓                            | ✓                             |
| GAD-7            | ✓                                          | ✓                            | ✓                            | ✓                            | ✓                             |
| SHAPS            | ✓                                          |                              |                              | ✓                            | ✓                             |
| PDQ-5            | ✓                                          |                              |                              | ✓                            | ✓                             |
| SF-12            | ✓                                          |                              |                              | ✓                            | ✓                             |
| WSAS             | ✓                                          |                              |                              | ✓                            | ✓                             |

|                                                    |   |  |  |   |   |
|----------------------------------------------------|---|--|--|---|---|
| PILT                                               | ✓ |  |  | ✓ | ✓ |
| Substance use and health-related absence from work | ✓ |  |  | ✓ | ✓ |
| Weight                                             | ✓ |  |  | ✓ | ✓ |
| Height                                             | ✓ |  |  |   |   |
| Saliva/Stool samples                               | ✓ |  |  | ✓ |   |
| Interview                                          |   |  |  |   | ✓ |

Note: PHQ-9, Patient Health Questionnaire-9; GAD-7, General Anxiety Disorder Scale; SHAPS, Snaith-Hamilton Pleasure Scale; PDQ-5, Perceived deficits questionnaire-5-item; SF-12, SF Short-Form 12 Health Survey; WSAS, Work and Social Adjustment Scale; PILT, Probabilistic instrumental learning task.

### 3. Biological Sample Handling

All participants will be asked to give saliva and stool samples. Saliva samples will be returned to Medicecks (a company that has been previously approved by the University of Oxford as a third-party supplier) for analysis; Stool samples will be returned to the Oxford Centre for Microbiome Studies, where they will be stored until analysis. The centre has an HTA licence for storage (Ref. 12217) of human samples but the samples will be destroyed after batch analysis.

All saliva and stool kits come with postage-paid return envelopes provided by the laboratory responsible for testing. Return envelopes do not require participants to disclose their personal information. Participants' samples will be labelled with their study ID in place of their name and study name on the test kit so they are not identifiable. When the saliva and stool test kits are used, in order to send them to the laboratory and have them processed, no identifying participant information will be shared with the laboratory, as they will be identified with the study ID only.

Urine samples will be tested at home by the participants in the ketogenic diet as a self-monitoring aid. Participants will use a dipstick and the result recorded. The urine will be tipped down the toilet after testing.

### 4. Will the research include any audio, video or photographic recordings?

Yes. The interviews for participants will be conducted after the 12-week follow-up via secure, encrypted software licensed by the university (Microsoft Teams), and the interviews will be audio-recorded at the consent of the participant to help with summarising the findings (**Appendix 16**). The cameras of the interviewer and the participant will be turned off. Data will be securely kept in a password-protected University shared drive with access restricted to the research team. Some qualitative interviews with participants in the ketogenic diet arm will be transcribed verbatim by Microsoft Teams recording facility to help create quotes. The recordings will be deleted once interviews have been transcribed and the transcripts have been checked for accuracy and clarity, and data analysis completed.

### 5. Discontinuation/Withdrawal of Participants

If the participant meets any one of the following conditions, the Investigator will stop the treatment at his/her discretion. The participant, however, will not be considered to have dropped out of the study. This may happen for several reasons, including but not limited to:

- a. The participant wishes to stop the treatment.

- b. The Investigator judges that it is difficult to continue the treatment because of emergence of serious adverse events (SAE) as defined below.
- c. The Investigator judges that the risk outweighs benefit in continuing the treatment.
- d. The participant in the KD arm becomes pregnant.
- e. The Investigator judges that it is inappropriate to continue the treatment for other reasons, such as bereavement.

If a participant wishes to withdraw from follow-up, data collected up to the point of withdrawal will still be used, as detailed in the ePIS. The reason for follow-up withdrawal, if provided, will be recorded on the eCRF. No participants will be replaced if they discontinue treatment or withdraw from follow-up.

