#### Formulation, dose and route of administration for research

4:1 (fat: protein + carbohydrates) pre-prepared KD meals (3 meals per day) and snacks without energy restriction. Each nutritional counselling session typically lasts 20-30 minutes.

In this study, a registered dietitian will contact participants to enquire about their current diet and provide advice on how to change it. Participants will be offered and encouraged to use pre-packaged meals from a commercial ketogenic diet supplier to enhance adherence and reduce the burden on participants. However, participants will be free to mix and match appropriate non-packaged food or additional ketogenic foods in their diet in consultation with the dietitian. The dietitian will provide weekly support for up to 30 minutes and enquire about issues and experiences, troubleshooting as necessary, and provide guidance on how to prevent or overcome side effects of KD diets, and keep record of the participant's ketosis level. As the diet progresses, if the participant wishes to continue following the diet, the dietitian

|                                                                                             |                                                                                                                                                                                                                                                                                                                                                                                                                                                                                                                                                                                                                                                                                                                                                                                                                                                                                                                                                                                                                                                                                                                                                                       |

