## 2. Reporting procedures for serious adverse events or reactions

Only a serious adverse event (SAE) occurring to a participant will be collected in this study. Reports of related (resulted from administration of any of the research procedures) and unexpected (the type of event is not listed in the protocol as an expected occurrence) SAEs will be reported to the ethics committee and the study steering committee (SSC). For fatal and life-threatening suspected unexpected serious adverse reactions (SUSARs), this will be reported as soon as possible, but no later than 7 calendar days after the PI is first aware of the reaction. Any additional relevant information will be reported within 8 calendar days of the initial report. Non-fatal or non-life-threatening SUSARs will also be reported as soon as possible, and no later than 15 days after the PI is first aware of the reaction.

AEs that are not serious will not be collected, as they offer no scientific value in our case, and have been extensively collected and reported in previous studies of ketogenic diets and are well known. Collecting only SAEs will reduce

the burden to participants such as life-threatening events, incidents resulting in persistent or significant disability/incapacity.

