## 9. ADVERSE EVENTS

Only a serious adverse event (SAE) occurring to a participant will be collected in this study. Serious adverse events will be presented descriptively

- classified by types,
- the relevance of this SAE to the treatment

We will report serious adverse events (SAEs) only, reporting the total number and the total number of people affected by the arm. We expect these to be very rare and will not use inferential statistics.

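### The plan does not say that the date of, or reason for, stopping the assigned diet is recorded, and non-serious adverse events are not collected, so stops due to side effects cannot be reported by arm

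*Combined protocol and SAP*

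**What the plan says.** Protocol Section G.5 lists five circumstances, (a) to (e), in which the assigned treatment may be stopped. Of a person who stops, it says: "The participant, however, will not be considered to have dropped out of the study". Two of the five matter here. Item (a) is "The participant wishes to stop the treatment", with no mention of asking or noting why. Item (c) is "The Investigator judges that the risk outweighs benefit in continuing the treatment", which is separate from the item on serious adverse events. G.5 then turns to people who leave follow-up, and only there mentions a record: "The reason for follow-up withdrawal, if provided, will be recorded on the eCRF".

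On harms, Section I.2 states "AEs that are not serious will not be collected, as they offer no scientific value in our case". Its reasons are that these effects are well documented in earlier ketogenic-diet studies and that participants are spared burden. SAP section 9 follows suit: "We will report serious adverse events (SAEs) only, reporting the total number and the total number of people affected by the arm".

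Section H describes weekly calls in the ketogenic arm at which the dietitian asks about problems and should "provide guidance on how to prevent or overcome side effects of KD diets". The record mentioned for those calls is the ketosis result. SAP section 4.4 lists the process outcomes: sessions attended, weekly adherence ratings, ketone levels, continuation at week 12 and satisfaction at week 6. Stopping the diet, with or without a reason, is not among them.

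**The concern.** The side effects that the protocol expects from the diet (Section C, item 10, and Section H), such as nausea, fatigue and constipation, are described as mostly mild and transient. They would ordinarily fall below the SAE threshold. They are also the events most likely to make someone give up the diet. The plan excludes them from collection and does not say that the decision to stop, or its cause, is written down.

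Two things are at stake. First, a report of few or no SAEs could be read as good tolerability even if a number of people had stopped because of side effects. Second, Section C calls this a proof-of-concept trial. If the intention-to-treat effect is small, readers will ask whether the diet did not work or whether people could not stay on it. Knowing who stopped, when and why bears directly on that question.

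**Working it through.** This is mainly a check of the text. The plan gives no figure on this point to reproduce.

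**Step 1. What is recorded for each event**

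| Event | Date or reason recorded? | Source |
|---|---|---|
| Leaves follow-up | Reason, if given, on the eCRF | Protocol G.5 |
| Stops the assigned diet, stays in follow-up | Not stated | Protocol G.5; SAP 4.4 silent |
| SAE | Yes, prompted weekly in both arms | Protocol I.1; SAP 9 |
| Non-serious side effect | Expressly not collected | Protocol I.2 |
| Ketosis result | Yes, by the dietitian | Protocol Section H |

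Where the protocol intends a record it generally says so. For the second row it does not, and for the fourth it says the opposite.

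**Step 2. Following one participant through the plan.** Take someone in the ketogenic arm who stops in week 2 because of nausea.

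- The weekly adherence rating falls, and attendance may fall.
- Under SAP section 3.2, anyone responding to fewer than 5 of up to 6 calls counts as non-adherent. This person can therefore land in the same category as someone who disliked the meals or simply missed calls.
- The week-6 satisfaction items may show whether the food was enjoyed, and the week-12 item whether the diet is still being followed. Neither asks for the cause of stopping.
- The interviews cover about 20 people chosen for a range of adherence and response (Section G.2), so they cannot supply a rate by arm.

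No planned output gives the number who stopped because of side effects, in either arm. Worsening mood is different: PHQ-9 and GAD-7 continue at weeks 2, 4, 6 and 12 after the diet is stopped, so it would be seen.

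**Step 3. Possible scale.** SAP section 2.2 reports 88 randomised, and allocation was 1:1, so about 88 / 2 = 44 per arm. The documents give no rate of stopping for side effects, so these rates are assumptions:

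- 10%: 44 × 0.10 = 4.4, about 4 people
- 20%: 44 × 0.20 = 8.8, about 9 people
- 30%: 44 × 0.30 = 13.2, about 13 people

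**Step 4. What few SAEs would show.** With zero SAEs in 44 people, the one-sided 95% upper limit p solves (1 − p)^44 = 0.05, so p = 1 − 0.05^(1/44) = 0.066, or 6.6%. This limit concerns serious events only. It does not measure tolerability, and a low SAE count does not stand in for the missing reasons.

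**Step 5. Related conflicts in the text.** Protocol Section J.4 plans to compare adverse events between arms as proportions with Fisher's exact test. Section I.2 collects only SAEs, and SAP section 9 reports them descriptively with no inferential test. Even if Section J.4 means SAEs, the test conflicts with the SAP. Separately, the opening sentence of G.5 words stopping both as something the investigator will do and as something left to discretion.

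**The case against.** Collecting only SAEs is an explicit choice with stated reasons: earlier evidence and participant burden. The background review in Section E, which found no controlled trials in mental disorders, is about efficacy and does not rebut that choice. This stands as a reason not to ask for full adverse-event collection. It does not supply the missing item, because earlier studies may show which symptoms occur but not how many people in each arm of this trial stopped because of them.

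Three stronger readings are tempting and are not supported.

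- A reader might infer that item (c) in G.5 has no data to act on. It is a discretionary judgement. The investigator can draw on SAEs prompted at each weekly call, the weekly enquiry in the ketogenic arm, PHQ-9 every two weeks with a call triggered by the suicide item, and clinicians who respond to untoward events (Section I.3). What the plan lacks is a systematic record below the SAE threshold, and it describes no side-effect enquiry in the control arm.
- A reader might infer that the trial cannot report tolerability at all. Attendance, adherence, continuation, satisfaction and interviews are planned and are informative, though indirect.
- A reader might infer that reasons for stopping are certainly not recorded. The eCRF and call scripts are not in the supplied text and the CONSORT figure is not shown. The supportable statement is that the plan does not say they are recorded.

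Nor do the documents show that the steering committee would be blind to a cluster of stops. Section L.2 gives it accruing data, and safety monitoring if required.

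Finally, recruitment had already stopped when the SAP was finalised, so some of this information may be recoverable only from notes. That limits what the fix can deliver.

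**Conclusion.** The point holds as a gap in harms reporting, and it is worth closing because closing it is cheap. The protocol separates stopping the diet from leaving follow-up, provides for a reason only for the latter, and affirmatively excludes non-serious events. Taken together these provisions leave discontinuation due to side effects, and side-effect rates, unreportable by arm.

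The size is unknown. The range of 4 to 13 people in the ketogenic arm rests wholly on assumed stopping rates of 10% to 30% and on about 44 per arm. The primary estimate is not affected; its interpretation is, if the effect is small. The conclusion assumes that the eCRF and call forms, which cannot be seen here, have no such field. If they do, only the protocol wording and the SAP table need adding.

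**What to change.** 1. In protocol Section G.5, add an eCRF field for both arms giving the date the assigned diet was stopped and the main reason, including side effect with the symptom named. Complete it from the existing weekly calls, or from call notes where calls are finished.
2. In Section I.2, exempt events that lead to stopping the diet from the rule against collecting non-serious events.
3. In SAP sections 4.4 and 9, add a table of stops by arm and reason, and share it with the steering committee.
4. Where reasons cannot be recovered, state this as a limitation and do not infer good tolerability from a low SAE count.
5. Reconcile the Fisher's exact comparison in Section J.4 with Section I.2 and SAP section 9, and reconcile the mandatory and discretionary wording in the first sentence of G.5. No change to the clinical stopping rules is proposed.

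The cost is one short form entry, a few minutes of staff time per person who stops, and one table, with no new participant contacts. The downside is that retrospective entries may be incomplete because recruitment has ended.

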## 6. Definition of End of Study

The end of study is set as the date of resolution of the last data query.

## 7. Please detail all expenses or gifts that will be offered to participants.

All participants will be reimbursed for their time and effort after each fully completed assessment after baseline (vouchers = £10 at week 2 and week 4; £30 at week 6; £30 at week 12; £10 qualitative interview after week 12). A pro-rated £10 gift voucher will be offered to the participant for partial completion where PHQ-9 (primary outcome) is the only measurement administered over the phone. Participants randomised to the control group will receive £20 shopping vouchers every two weeks to purchase vegetables and fat replacement. Participants in the ketogenic diet group will receive food to support dietary adherence.

## Section H. Interventions

### Drug/Substance 1

#### Name of drug/substance to be used

A 4:1 (fat: protein+carbohydrates) pre-prepared KD meals and snacks with weekly KD-focused nutritional counselling

#### Formulation, dose and route of administration for research

4:1 (fat: protein + carbohydrates) pre-prepared KD meals (3 meals per day) and snacks without energy restriction. Each nutritional counselling session typically lasts 20-30 minutes.

In this study, a registered dietitian will contact participants to enquire about their current diet and provide advice on how to change it. Participants will be offered and encouraged to use pre-packaged meals from a commercial ketogenic diet supplier to enhance adherence and reduce the burden on participants. However, participants will be free to mix and match appropriate non-packaged food or additional ketogenic foods in their diet in consultation with the dietitian. The dietitian will provide weekly support for up to 30 minutes and enquire about issues and experiences, troubleshooting as necessary, and provide guidance on how to prevent or overcome side effects of KD diets, and keep record of the participant's ketosis level. As the diet progresses, if the participant wishes to continue following the diet, the dietitian

|                                                                                             |                                                                                                                                                                                                                                                                                                                                                                                                                                                                                                                                                                                                                                                                                                                                                                                                                                                                                                                                                                                                                                                                                                                                                                       |
|---------------------------------------------------------------------------------------------|-----------------------------------------------------------------------------------------------------------------------------------------------------------------------------------------------------------------------------------------------------------------------------------------------------------------------------------------------------------------------------------------------------------------------------------------------------------------------------------------------------------------------------------------------------------------------------------------------------------------------------------------------------------------------------------------------------------------------------------------------------------------------------------------------------------------------------------------------------------------------------------------------------------------------------------------------------------------------------------------------------------------------------------------------------------------------------------------------------------------------------------------------------------------------|
|                                                                                             | 
and participant will work on how to transition away from pre-packaged foods.
 
The foods require storing in a fridge and will be sent a week at a time so will require some space to store them.
 
Previous studies of the KD intervention have reported mostly mild and transient side effects, commonly referred to as "keto flu". These side effects may appear two to seven days after starting a ketogenic diet, including headache, foggy brain, fatigue, irritability, nausea, difficulty sleeping, and constipation. These symptoms usually disappear by themselves. The team will also provide a pamphlet explaining the benefits and risks associated with the study and KD meals, as well as offer solutions to any problems that may arise (APPENDIX 9. Dietary materials for the intervention group).
 
We also provide home urine test strips for ketosis and ask participants to measure ketosis at least twice a week. The main purpose is to reassure the participant and the dietitian that they are in ketosis. The dietitian will record these results, as it is evidence that the participant has achieved ketosis.
 |
| Duration of treatment for research                                                   | 6 weeks                                                                                                                                                                                                                                                                                                                                                                                                                                                                                                                                                                                                                                                                                                                                                                                                                                                                                                                                                                                                                                                                                                                                                               |
| Licence status of this drug/substance                                                | N/A                                                                                                                                                                                                                                                                                                                                                                                                                                                                                                                                                                                                                                                                                                                                                                                                                                                                                                                                                                                                                                                                                                                                                                   |
| Usual Indication                                                                     | Used for treatment of diabetes, weight loss, treatment of epilepsy or other reasons usually at people's own instigation.                                                                                                                                                                                                                                                                                                                                                                                                                                                                                                                                                                                                                                                                                                                                                                                                                                                                                                                                                                                                                                              |
| Usual Dose                                                                           | 3 meals with snacks per day without energy restriction                                                                                                                                                                                                                                                                                                                                                                                                                                                                                                                                                                                                                                                                                                                                                                                                                                                                                                                                                                                                                                                                                                                |
| Usual duration of treatment                                                          | 6 weeks                                                                                                                                                                                                                                                                                                                                                                                                                                                                                                                                                                                                                                                                                                                                                                                                                                                                                                                                                                                                                                                                                                                                                               |
| Where will drug/substance be sourced from?                                           | Meal providers for NHS services                                                                                                                                                                                                                                                                                                                                                                                                                                                                                                                                                                                                                                                                                                                                                                                                                                                                                                                                                                                                                                                                                                                                       |
| Where will drug/substance be stored at site?                                         | It will be prepared by a company in the UK                                                                                                                                                                                                                                                                                                                                                                                                                                                                                                                                                                                                                                                                                                                                                                                                                                                                                                                                                                                                                                                                                                                            |
| How will drug/substance be dispensed?                                                | Meals and snacks will be directly shipped to the participant's address and stored by the participant, mostly out of a fridge.                                                                                                                                                                                                                                                                                                                                                                                                                                                                                                                                                                                                                                                                                                                                                                                                                                                                                                                                                                                                                                         |
| How will the drug/substance be prepared by the researchers for use in this research? | N/A                                                                                                                                                                                                                                                                                                                                                                                                                                                                                                                                                                                                                                                                                                                                                                                                                                                                                                                                                                                                                                                                                                                                                                   |

| Section I. Safety         |                                                                                                                                                                                     |
|---------------------------|-------------------------------------------------------------------------------------------------------------------------------------------------------------------------------------|
| 1. Definitions            |                                                                                                                                                                                     |
| Adverse Event (AE) | Any untoward medical occurrence in a participant to whom a substance has been administered, including occurrences which are not necessarily caused by or related to that substance. |

|                                                              |                                                                                                                                                                                                                                                                                                                                                                                                                                                                                                                                                                                                                                                                                                                                                                                                                                                                                                                                                                                                                                                                                                                                                                                                                                                                                                                                                                                                                                |
